### Outcomes

The primary outcomes for Aim 1 for survivors consist of:*Use of safety strategies*: The Safety Behavior Checklist adapted from Sullivan & Bybee [40] and Parker & colleagues [41] measures the range of strategies used by survivors to halt or escape violence. This instrument asks if each strategy has been used over the last 6 months and if the strategy was helpful in dealing with the abusive partner or abuse. The checklist includes use of formal services (e.g., Have you met/called/texted/instant messaged a professional that works on campus (e.g. a professor, campus administrator, campus staff at a women’s center or campus health clinic) about your partner hurting you (physically, sexually, or emotionally?, Did you get/try to get an order of protection (or restraining order) against your partner?) and informal safety steps (e.g., Have you developed a code/signal so others would know when you were in danger from your partner?, Have you identified a safe place on campus or in the community you could go if your partner became dangerous?). The percent of safety behaviors tried by survivor that she found helpful will be the primary outcome.*Decisional conflict immediately post intervention*: The decision process for survivors is measured with questions adapted from validated subscales of the Decisional Conflict Scale (DCS) [42, 43]. The DCS tests whether using this safety planning decision aid helps a woman to understand the advantages and disadvantages of safety planning options and to know her values related to them. The Decisional Conflict Scale discriminates between people who make decisions and those who delay making decisions. The DCS consists of twelve items (e.g., “I know the risks of taking steps to increase my safety in my relationship”, “I am clear about which benefits of the relationship are most important to me”, “I have enough support from others to make decisions about my safety”) with a 5-point likert response scale from ‘strongly agree’ to ‘strongly disagree’. The DCS provides a total score, which is a measure of the decision process, as well as scores for four subscales (feeling informed, certainty about decision, values clarity, and support), with higher scores on the DCS indicating a greater degree of decisional conflict (indicative of a poorer decision process) [39, 40]. Decisional conflict will be measured pre and post the first use of the decision aid.

The secondary outcomes for Aim 1 for survivors consist of:(c)*IPV exposure*: The Composite Abuse Scale (CAS) is a 30-item validated comprehensive intimate partner violence screening measure with strong psychometric properties [48, 49]. The CAS measures 4 dimensions: Severe Combined Abuse, Emotional Abuse, Physical Abuse, and Harassment. This project will use an adapted response scale: “never, only once, several times or many times” and participants will be asked how often their partner did any of the items in the last 6 months. Example items include: “Told me I was stupid”, “Pushed, grabbed or shoved me”, “Followed me”, “Made me have sex when I didn’t want to”.(d)*Mental health*: Depression is measured with the Center for Epidemiologic Studies Depression Scale, Revised (CESD-R) [44, 45]. A 20-item self-report measure screens for depressive symptoms in community samples. Items are rated based on frequency in the ‘past week or so’ from 0 (Rarely or none of the time—less than one day) to 4 (Nearly every day for two weeks). The CESD-R is a revision of the widely-used and validated CESD, with revisions reflecting DSM-IV criteria for depression. The revised CESD correlates highly with the original, demonstrates good to excellent face and construct validity and excellent internal consistency [44–46].(e)*Drug and alcohol abuse*: A modified version of the Monitoring the Future Drug and Alcohol Questionnaire is used to measure alcohol and drug use. Participants are asked to self-report on how many occasions they have used alcohol in the last 30 days and in the last 6 months, as well as binge drinking behavior. Participants are also asked on how many occasions they have used drugs, broken down into 5 categories (marijuana, club drugs/hallucinogens, stimulants/narcotics, prescription drugs, other) in the last 30 days and last 6 months. [47](f)*Decisional conflict at 6 and 12 months*: In addition to measuring decisional conflict outcomes immediately post intervention, decisional conflict outcomes will be assessed at six and 12 months.

The primary outcomes for Aim 2 for friends of survivors consist of:*Intimate partner violence awareness*: Friends’ awareness of IPV is measured by a 3 scales: 1) Acceptance of General Dating Violence Scale [48], is a five item scale (e.g., There are times in a dating/intimate relationship when violence is okay, Someone who makes their partner jealous on purpose deserves to be hit) with responses on a 4 point scale from strongly disagree to strongly agree; 2) Knowledge of IPV myths is measured with 5 items developed by the research team (E.g. Leaving an abusive partner will stop the abuse, women can’t be abused by a female partner) with responses on a 4 point scale from strongly disagree to strongly agree; and 3) Perception of IPV Awareness and Seriousness are measured with 2 items developed by our team, adapted from items from Beeble et. al [49] (“In your opinion, how *common* are abusive dating/intimate relationships in college? very uncommon, uncommon, happens sometimes, common, very common”, “In your opinion, how *potentially serious* (damaging, harmful, or dangerous) are abusive relationships in college? no potential for danger or harm, generally don’t cause much harm, can have some harmful effects, have harmful effects but generally not serious, potentially very serious or dangerous”).*Confidence to intervene*: Friends’ efficacy to intervene is measured with adaptation of Self-efficacy to Deal with Violence Scale [50] used with adolescents, adapted to assess friends of survivors’ confidence to intervene. The 19-item measure assesses how confident a person feels that they can address relationship issues on a 4 point scale (“not at all confident, somewhat confident, confident, very confident”. Example items include: “How confident are you in your ability to… start a conversation with a friend regarding worrisome behaviors by her partner/ex-partner”, “…identify appropriate/useful resources/people on your campus to help a friend in an unhealthy or unsafe relationship?”.*Friends’ supportive behaviors*: Supportive behaviors are measured with a checklist adapted from multiple sources, including Sullivan & Bybee [40] and Parker & colleagues [41] and from the literature around family/friend responses as described by survivors and engagement behaviors from Latta and Goodman’s [51] model and Beeble et al.’s [49] Approaches to Helping measure. Items ask about what the participant has done to support a friend in an abusive relationship (e.g. let her stay with you for safety reasons, gave her information about relationship abuse resources such as a hotline) and if each behavior was perceived as helpful to the friend.*Decisional conflict immediately post intervention*: The decision process for friends is measured with questions adapted from validated subscales of the Decisional Conflict Scale (DCS) [42, 43] used for survivors for Aim 1. The 12 items test whether using this safety decision aid helps a friend to understand the advantages and disadvantages of options for helping their friend in an abusive relationship, and to know his/her values related to those options (e.g., “I know my options for helping my friend who is in an unhealthy relationship.”, “I am clear about which reasons for helping my friend are most important to me.”, “I have enough advice to make decisions about helping my friend who is in an unhealthy relationship.”

The secondary outcomes for Aim 2 for friends consist of:*Intimate partner violence awareness*: Friends’ awareness of IPV is measured by 3 scales: 1) Acceptance of General Dating Violence Scale [48], a five item scale (e.g., There are times in a dating/intimate relationship when violence is okay, Someone who makes their partner jealous on purpose deserves to be hit) with responses on a 4 point scale from strongly disagree to strongly agree; 2) Knowledge of IPV myths is measured with 5 items developed by the research team (E.g. Leaving an abusive partner will stop the abuse, women can’t be abused by a female partner) with responses on a 4 point scale from strongly disagree to strongly agree; and 3) Perception of IPV Awareness and Seriousness are measured with 2 items developed by our team, adapted from items from Beeble et. al [49] (“In your opinion, how *common* are abusive dating/intimate relationships in college? very uncommon, uncommon, happens sometimes, common, very common”, “In your opinion, how *potentially serious* (damaging, harmful, or dangerous) are abusive relationships in college? no potential for danger or harm, generally don’t cause much harm, can have some harmful effects, have harmful effects but generally not serious, potentially very serious or dangerous”).*Decisional conflict at 6 and 12 months*: In addition to measuring friends’ decisional conflict outcomes immediately post intervention, decisional conflict outcomes will be assessed at six and 12 months.

### Description of the MyPlan intervention App

After completing the measures in the App, the participant will then be directed to the next section of the App, the MyPlan intervention. For both friends and survivors, the intervention starts by listing information about common IPV myths, and then describes characteristics of healthy relationships. Next the participant is directed to the “My Safety” section, which is the Danger Assessment (DA) or the DA-Revised (for women abused by a female partner). The risk-assessment consists of self-report items on validated risk factors for repeat violence and lethal IPV, such as an increase in severity and frequency of violence, controlling behavior, jealousy, use of alcohol/drugs, and forced sex [52]. A weighted scoring algorithm provides an instant DA score (range 0–38) graphically with narrative on the level of danger [53, 54]. For example, the score is converted to the validated levels of danger such as: 1) variable danger (low risk, but situations change quickly, a score of less than 8); 2) increased danger (a score of 8–13); 3) severe danger (a score of 14–17); and 4) extreme danger (a score of 18 and above) [54]. The participant is provided with personalized messages about their danger based on their score. For friends, this section is titled “My Friend’s Safety” and the section includes the DA or DA-R, the friend will respond to the risk factors based on what they know/observe in their friends’ relationship. They will not likely be able to answer some of the questions, for example, “the partner forces her to have sex”, and therefore, the true risk is under-estimated. However, in our previous research using the DA to validate risk of severe violence/lethality, assessment of danger in the relationship by a friend/family member is consistent with reports by the abused woman herself [52]. Next, the App includes “My Priorities,” an interactive visual aid that allows users to set priorities for safety. A clickable “sliding bar” allows the woman to make pairwise comparisons of importance between priorities including privacy, feelings for partner, severity of violence, well-being of children and social support/status. These are then combined mathematically to generate priority weights. For friends, priorities include concern for friend’s safety, privacy, personal safety and social support/status. After setting priorities, participants receive a personalized graph with the results. Next, the woman/friend moves to “My Plan,” personalized with messages based on responses in the previous sections. For example, if a woman indicates in the “My Safety” section that her partner has stalked her, the personalized safety plan messages will include detailed information about stalking and resources available to increase her safety. For friends, the “My Plan” section includes personalized messages on how to privately discuss concerns and provide campus and off-campus resources that can be useful to support their friend. We will collect information on women’s/friend’s use of the App, including number of times the App is accessed, time spent using the App, and content accessed, for example.

### Description of the generic IPV resource App (Control App)

The control App is based on usual safety planning services college women and friends have access to on-campus and on the Internet through IPV websites. We will not use the DA or DA-R for risk assessment in the relationship as these are specific components of the safety decision App intervention, but we will assess risk factors for severe violence as identified on IPV websites (such as the Red Flag Campaign). The control group App will provide women and friends with brief safety planning information and IPV resources targeted to college students age 18–24 years. The control group App safety plan is not personalized to women’s/friends’ safety priorities and danger in the relationship. As detailed above, we will collect information on women’s/friend’s use of the control App, including number of times the App is accessed, time spent using the App, and content accessed.

### Follow-up sessions

Follow-up App sessions for both groups will be conducted at 6 and 12 months post-baseline. These time points are selected for several reasons, including findings from previous research that IPV frequency and severity often increases over the course of a violent relationship, making it important that participants have access to the App to input changes in risk factors for IPV and review their safety plan at multiple time points [20]. Further, follow-up contacts provide important opportunities for the RAs and study participants to reconnect related to the study and supports retention of participants that may have to relocate for safety. Participants will be encouraged by email, text and phone contact by the RA to access the password-protected App to complete the session and follow-up assessment. As noted above, for all outreach to participants, the RA will use safe contact information and preferred mode of communication provided by the participant. The post-baseline data collection will consist of the same questions collected at baseline but will focus on outcomes since the previous session. For example, participants will be asked about threatened or actual IPV since the previous session/assessment.

### Retention

Several methods used by the research team have proven valuable in retention of participants in longitudinal studies [55–58]. All retention activities will be adjusted to meet the safety needs of the participant, on an individualized basis. Retention strategies include:Asking participant at enrollment for several (at least two) names, phone numbers, e-mails of individuals (i.e., friends, roommate, resident assistant, campus staff, coach) who would know of their whereabouts and could be used as alternate safe contacts. We will also ask if texting and leaving a message for each phone number is safe. As part of each email, text or telephone contact the participant receives from the RA, she/he is provided with study contact information;Safely contacting participants throughout the study, this includes contacts in-between (2, 4, 8, 10 months) the scheduled post-baseline sessions to briefly assess for safety, confirm contact information, and ascertain any anticipated changes to contact information;Using a safe email address, an automated email is sent to the participant announcing a follow up App session (6 or 12-month) is due. The window opens and this email is sent 2 weeks before the 6 and 12-month follow up due date. If follow up at 6 or 12 month is not completed within 1 week of first email announcing follow up is due, an auto reminder email is triggered, followed by manual reminders from the RA via email (3 attempts) then text/phone (up to 5 attempts, up to 3 messages left). If unable to reach the participant via direct contact info, the RA will attempt to contact alternate contacts (family, friends listed up to 2 times each). The follow up window closes and reminders cease 6 weeks after sending the 6 or 12-month follow up due email;Providing compensation to each participant for his or her time and expertise. Compensation for baseline ($20), 6-month ($30) and 12-month ($50) is a total of $100 for an estimated 3 hours of time, an amount consistent with other studies;Use of a secure study database for organizing participant contact information and study schedule.

## Data analyses

Before any analyses are carried out, the data will be audited for quality and completeness, including missing data patterns, evaluation of distributions for outliers in quantitative data, and checking distributions of variables to ensure that they meet the assumptions of planned analyses. Chi-square tests for categorical variables and t-tests for continuous variables will be used to test for differences between the safety intervention and control groups on baseline variables that are potential confounding variables. These included relationship status (dichotomous: currently residing with the abuser or not); language (English or Spanish), baseline knowledge of safety options (continuous); clarity of safety preferences (continuous); perception of support (continuous); computer experience (continuous). Variables for which significant differences are found will be included as covariates in the analyses where appropriate. All analyses will use intent-to-treat principles.

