### Accessing the App

Upon obtaining informed consent, collecting safety contact information, enrolling participants and entering their information into the secure study database, participants will be randomly assigned to intervention or control groups using a computerized stratified blocked randomization scheme. Randomization occurs automatically at the time of enrollment via a randomization algorithm. Participants will be randomized to complete either the MyPlan Intervention App or the Generic IVP Resource App (control). Stratification is based on state of residence (Maryland or Oregon), type of participant (friend/survivor), survivor having children (child/no child in home), and type of school (two year technical school, community college, four year state college or university, four year private college or university, or other). Blocked design will ensure that the proportion of women/friends in Maryland and Oregon assigned to one group or the other remains relatively constant throughout the study. Once the participant is randomized, an automated email from the RA will be sent to the participants’ safe email address containing the assigned (intervention or control) study App access instructions. The participant will have two options to access the App. The first option is to download the App to their smartphone from one of the major U.S. App stores, where it will be posted as a free App available to anyone with a smartphone. Once downloaded, the App is user and password-protected, like a bank App, preventing others not enrolled in the study (e.g., partners) from opening the App. The second access option is to use the smartphone’s or computer’s Internet browser to access a web-based version of the App via the study website. With either mode of access, users will enter an assigned username and password the first time the App is accessed. They will also be instructed to set a security PIN code as the primary means to access the app once logged in. Users can define any 4 digit code to be the PIN and if they need to reset the PIN, must first log out and then back in using their username and password. Participants will be instructed to remove the App once they have completed the session if unsafe to have on their device, though warned that it is not currently possible to delete apps from a purchase history. Data collected from participants is labeled as either study data or personal identifiers. In order to ensure the highest protection of privacy and security, all personal identifiers (only collected at study enrollment) are saved in a physically separate database in a HIPAA compliant network environment. Study data and personal identifiers are never combined during the course of the study. Detailed safety procedures have been developed and are explained in the Risks section.

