### Intervention effectiveness

Residualized change regressions will be used to test for significant differences between the intervention/control groups in change in decisional conflict. Change on the Decisional Conflict subscales, e.g., values or priorities clarification from pre-to post-use at the first session will be the dependent variable. Group (intervention vs. control), baseline decisional conflict and potential confounding variables for which intervention and control groups differ at baseline will be included in the model as independent variables. Longitudinal multilevel models will be used to examine change over time in women’s safety behaviors (percent of safety behavior tried that a survivor found helpful), IPV (measured by the CAS) and substance use (measured by AUDIT and DAST). Time (e.g. baseline, 6 months, and 12 months) will be used as a level 1 predictor of the dependent variable. The level 1 model yields an intercept and slope parameter for each person. The intercept reflects the baseline value on the dependent variable and the slope reflects the rate of change across time on the dependent variable. Group will be used as a level 2 predictor of slope parameter. Finding the group is a significant predictor of the level 1 slope parameters means that individual change over time differs for intervention and control groups. Potential confounding variables for which intervention and control groups are significantly different at baseline will be entered as level 2 covariates predicting individual change.

The same set of analyses described above will be used to examine change in friend’s awareness of IPV, decisional conflict, safety behaviors and confidence to intervene.

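### Covariates are chosen by baseline significance tests and the listed models leave out three randomisation strata, which costs precision but does not inflate the type I error

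*Protocol article*

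**What the plan says.** All places are in the protocol article.

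- **Data analyses** sets out the screening step: "Chi-square tests for categorical variables and t-tests for continuous variables will be used to test for differences between the safety intervention and control groups". The candidates are relationship status, language, knowledge of safety options, clarity of preferences, perceived support and computer experience. The rule that follows is "Variables for which significant differences are found will be included as covariates in the analyses where appropriate". No significance level for selection is given.
- **Intervention effectiveness** repeats the rule for both model families. For the residualized change regression: "Group (intervention vs. control), baseline decisional conflict and potential confounding variables for which intervention and control groups differ at baseline will be included". For the multilevel models: "Potential confounding variables for which intervention and control groups are significantly different at baseline will be entered as level 2 covariates predicting individual change". The other listed terms are group and time. The same analyses are planned for friends.
- **Accessing the App** describes the allocation: "Stratification is based on state of residence (Maryland or Oregon), type of participant (friend/survivor), survivor having children (child/no child in home), and type of school", with five school categories. State, child in home and school type are neither among the six candidates nor among the listed model terms. Participant type is covered, because survivors and friends are analysed separately.

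**The concern.** Allocation is by computer in stratified blocks, so any baseline difference between arms is due to chance. A test of that difference says nothing about whether the variable predicts safety behaviours, abuse exposure or decisional conflict, which is what makes adjustment worthwhile. The rule can admit an irrelevant variable because it happens to be unbalanced and drop a strong predictor because it happens to be balanced. The model is not known until the data are seen, and the qualifier at the end of the rule leaves further room for choice.

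Stratified randomisation also balances the arms on the stratification factors. A model without those factors leaves their variance in the residual, so the reported standard error is larger than the true variability of the estimate. What is at stake is precision in the primary analyses and a model fixed in advance.

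**Working it through.** **1. The plan's own figure.** Statistical power states 0.99 for 300 per group, f = 0.58, autocorrelation 0.3 and alpha 0.05. With noncentrality f²·N·m/(1-ρ) and m = 3 visits, 0.58² × 600 × 3 / 0.7 = 865, and power exceeds 0.999. If 0.58 is read as a standardised difference on a change score, d = 0.58/√1.4 = 0.49, and power is 1.000, 0.9997 and 0.997 at N = 600, 480 and 375. These agree with the stated 0.99, 0.99 and above 0.90. No covariate enters that calculation, so this point does not alter it.

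**2. Chance selection.** For six independent tests at 0.05 (assumed), 1 - 0.95⁶ = 0.265. At 0.10 it would be 1 - 0.9⁶ = 0.469. Knowledge, clarity and support resemble three of the four Decisional Conflict subscales described under Outcomes, so the tests are probably correlated and 0.265 is an upper figure at the 0.05 level.

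**3. Effect on a single-endpoint regression.** This is the form of the decisional-conflict analysis. Omitting strata that explain a share R² of residual variance inflates the standard error by 1/√(1-R²): 1/√0.95 = 1.026 and 1/√0.90 = 1.054.

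A simulation used 300 survivors, 2 × 2 × 5 = 20 strata, blocks of four, six independent covariates of which one is prognostic with r = 0.5, and 4,000 trials per row. Strata mix, block size, r and strata shares are assumptions. Without any other covariates, the mean standard error with strata omitted against included was 0.1154 against 0.1126 (ratio 1.025) at 5%, and 0.1154 against 0.1096 (1.053) at 10%, in line with the formula. Under no treatment effect, with nominal rejection 0.05:

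| Strata share | Plan's rule: rejection | SD of estimate | Mean SE | Prespecified: rejection | SD of estimate | Mean SE |
|---|---|---|---|---|---|---|
| 0% | 0.047 | 0.113 | 0.115 | 0.055 | 0.103 | 0.101 |
| 5% | 0.045 | 0.111 | 0.115 | 0.057 | 0.099 | 0.098 |
| 10% | 0.036 | 0.107 | 0.115 | 0.050 | 0.095 | 0.094 |
| 20% | 0.023 | 0.101 | 0.115 | 0.049 | 0.086 | 0.087 |

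The plan's rule never rejects too often. Its estimate is more variable than the prespecified one (0.111 against 0.099 at 5%). Much of that gap comes from the prognostic covariate, since it is already 0.113 against 0.103 when the strata explain nothing. At an assumed 0.3 SD effect, power was 0.754 against 0.885 (strata 10%, r = 0.5) and 0.735 against 0.787 (strata 5%, r = 0.3).

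**4. Effect on the group-by-time slope.** This is the form of the safety-behaviour analysis. Generalised least squares standard errors were computed for three equally spaced visits, complete data, 150 per arm, total variance 1 and within-person correlation 0.3. Strata shift the level only, so including them lowers the person-level variance from 0.30 to 0.25 (5%) or 0.20 (10%).

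- Group in both intercept and slope: 0.0683 with or without strata, so 0% inflation.
- Group in the slope only, as the text reads: 0.0531 against 0.0520 (2.0%) at 5%, and 0.0531 against 0.0508 (4.5%) at 10%.
- The same with a random-slope variance of 0.05: 1.6% and 3.6%.

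Stable stratum differences in level cancel from a within-person slope. Strata help that test fully only if they predict change as well as level.

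**The case against.** The strongest reply is that a journal article condenses the full protocol and that a list of terms is not a statement that nothing else enters. That carries some weight for the strata. It carries none for the selection rule, which is written out twice and applied to both model families. An analysis plan that followed this text would inherit the rule.

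Three stronger readings are tempting and are not supported:

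- **Selecting covariates on the data inflates false positives.** The simulated rejection rates are at or below 0.05. At a 5% strata share, 0.045 is within 1.5 Monte Carlo standard errors (√(0.05 × 0.95/4000) = 0.0034) of nominal. The clear departures appear at larger strata shares and are conservative.
- **Chance decides the primary model in one trial in four.** Group, time and baseline decisional conflict stay in their models throughout. Chance decides only whether a covariate is added, and 26% is an upper figure at the 0.05 level.
- **Leaving out the strata wastes 5-11% of the sample for every outcome.** Those figures (1/0.95 = 1.05, 1/0.90 = 1.11) belong to a single-endpoint model and do not carry over to the slope test.

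It is also true that the stated power is unaffected. At N = 300 the change-score version still gives 0.989. That rests on an effect size borrowed from a telephone intervention, so the lost precision would matter more if the real effect were smaller.

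**Conclusion.** The point stands as a matter of efficiency and prespecification. Baseline significance is the wrong criterion for adjustment: it makes the model data-dependent and leaves out prognostic variables that happen to be balanced. The listed models also omit state, child in home and school type. The consequence is lost precision and slightly conservative tests. The size depends on how prognostic these variables are, which the documents do not say. From omitting the strata alone, standard-error inflation is about 2.6-5.4% in the residualized change regression if they explain 5-10% of residual variance. For the group-by-time slope it is 0% to about 4.5% in the cases computed, depending on whether group also enters the intercept and whether strata predict change. If the strata are not prognostic this part is near zero, but the objection to the selection rule remains. The trial's validity is not in question.

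**What to change.** Delete the baseline significance tests and the selection rule from Data analyses and Intervention effectiveness. In their place, prespecify:

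- state, child in home (survivors only) and school type, with sparse school categories collapsed, as covariates in the decisional-conflict regression and as level 2 predictors of both intercept and slope in the multilevel models;
- baseline decisional conflict in its regression, as already planned;
- a short named list of prognostic baseline variables, for example drawn from the six candidates, used whatever their baseline p-values.

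The stratification data are already collected for allocation. Before any collapsing, the strata cost at most 1 + 1 + 4 = 6 parameters for survivors and 1 + 4 = 5 for friends in the regression, and twice that in the multilevel models. The rest is wording.
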